## Abstract

**Background:**

The Prime-Time Sister Circles® (PTSC) program is a multifaceted, community-based peer support intervention targeting African American women who are 40 to 75 years of age. It aims to reduce hypertension disparities observed among African American women by promoting adherence to antihypertensive therapies, including lifestyle modification and therapeutic regimens.

**Methods:**

The PTSC randomized controlled trial will evaluate the effectiveness of the PTSC Program on improved blood pressure control, healthcare utilization attributed to cardiovascular events, and healthcare costs. The study began in 2016 and will end in 2022. African American women who are 40–75 years old, have been diagnosed with hypertension, reside in Washington, D.C. or Baltimore, Maryland, and receive their care from Unity Health Care, a federally qualified health center in Washington, D.C., or Baltimore Medical System, a federally qualified health center in Baltimore, Maryland, are eligible to participate. Those randomized to the intervention group participate in the PTSC Program, which spans 13 weeks and comprises facilitator-led discussions, didactic training about hypertension management, and peer-based problem-solving concerning CVD risk factors and their amelioration. Blood pressure, weight, body mass index, waist circumference, self-reported adherence, physical activity, dietary practices, stress, and healthcare utilization data are collected at baseline, 13 weeks (end of the intervention), 9 months (months post-intervention), and 15 months (one year after the intervention). Healthcare costs will be computed at the end of the study. The study’s design is reported in the present manuscript, wherein we employed the SPIRIT checklist to guide its construction.

**Discussion:**

Disparities in hypertension prevalence and management observed among mid-life African American women exist as a result of a confluence of structural determinants of health. Consequently, there is a need to develop, implement, and evaluate culturally appropriate and relevant interventions that are tailored to their lived experiences. The PTSC Trial aims to assess the impact of the program on participants’ cardiovascular, psychosocial, and cost outcomes. Its results have implications for advancing the science of designing and implementing culturally relevant interventions for African American women.

**Trial registration:**

Unique identifier: NCT04371614. Retrospectively registered on April 30, 2020.

## Background

Hypertension affects approximately one-third of adults in the United States and significantly contributes to coronary heart disease, stroke, peripheral vascular disease, congestive heart failure, myocardial infarction, and renal failure [1, 2]. It is the single largest risk factor for cardiovascular mortality [3]. Non-Hispanic Black women are disproportionately encumbered by high blood pressure [4]. Recently, Chen and colleagues observed that Black women have the greatest cumulative risk of developing hypertension (86%) relative to White men (84%), Black men (85%), and White women (69%) [5]. Indeed, the prevalence of hypertension among African American (AA) women is 46.1%, the highest in the United States [6].

Hypertension disparities observed among AA women, particularly those aged 40 to 75 years of age, are rooted in a constellation of intrapersonal, interpersonal, health care system, and societal factors, whose intersection may adversely affect the degree to which adequate achievement and maintenance of blood pressure control occurs [7, 8]. Their presence suggests a strong need to identify effective strategies that attend to the confluence of unique sociocultural needs facing AA women, which may, in turn, enhance their capacity to manage their blood pressure successfully. One strategy for tackling uncontrolled hypertension among middle-aged AA women is the development and implementation of multi-component community-based interventions that promote therapeutic lifestyle changes [9, 10]. These interventions are typified by an emphasis on advancing culturally-rooted educational, behavioral, and psychosocial approaches to target modifiable CVD risk factors [11–14].

One such intervention is the Prime Time Sister Circles® (PTSC) Program, which addresses specific risk factors and barriers experienced by mid- to late-life AA women who have, or are at risk of developing, hypertension, with the goal of equipping program participants to manage their blood pressure through primary and secondary prevention strategies. There is indication to suggest that participation in the PTSC program is associated with increased physical activity; improved dietary patterns; reduced blood pressure, weight, and self-reported stress; and increased blood pressure self-monitoring, health screenings, and engagement in strategies geared toward psychosocial health [15, 16]. While previous investigations of the program employed quasi-experimental designs to discern its impact on clinical, behavioral, and psychosocial factors CVD risk factors, the use of more rigorous study designs to determine the effectiveness of the PTSC program is warranted.

Consequently, we have designed and are currently implementing a randomized controlled trial (RCT) to evaluate the association between exposure to the PTSC program and participants’ cardiovascular outcomes. The purpose of this paper is to describe this trial, the PTSC-RCT, which will ascertain the extent to which the PTSC program improves participants’ outcomes related to CVD risk factors, including education (knowledge about hypertension sequelae), behavioral (self-reported adherence), psychosocial (i.e., stress management and self-efficacy to manage blood pressure), clinical (blood pressure control, waist circumference, and BMI), and avoidable healthcare utilization (hospitalizations and inpatient admissions) attributable to CVD risk factors among AA women aged 40 to 75 years old residing in metropolitan Washington, D.C. or Baltimore, Maryland.

## Methods

The protocol’s flow is delineated in the CONSORT Diagram (Fig. 1) and the SPIRIT Flow Diagram (Fig. 2). We provide additional details about the PTSC trial below.

**Fig. 1 Fig1:**
[figure not shown]
CONSORT Flow Diagram [1]

**Fig. 2 Fig2:**
[figure not shown]
SPIRIT Flow Diagram of the PTSC-RCT Protocol

### PTSC program overview

The PTSC Program is a multifaceted, theoretically-driven, community-based peer support intervention targeting AA women who are 40 to 75 years of age. It was developed by two mid-life AA women, Drs. [name], a physician, and [name], a clinical psychologist, and established through the auspices of The Gaston and Porter Health Improvement Center, Inc. (GPHIC). The GPHIC’s National Training Institute trains PTSC facilitators on cardiovascular conditions, group facilitation and leadership skills, and the cultural beliefs undergirding self-management of chronic conditions. The facilitators are PTSC program graduates who live in the communities served by the program.

The PTSC program occurs over 13 weeks. Each facilitator-led Sister Circle includes 25 to 30 women. Each session lasts for 2 h and are held in accessible community sites (e.g., churches, public housing). Sister Circles are characterized by didactic training, guided discussions, and role-playing exercises that address CVD risk factors and strategies to overcome them. Facilitators follow a curriculum designed by the GPHIC that complies with The National Standards for Culturally and Linguistically Appropriate Services in Health and Health Care [17, 18]. The curriculum and its associated materials use text and illustrations to enhance knowledge uptake among women with varying literacy levels.

The PTSC Program draws from three theoretical frameworks: the social cognitive theory [19], the transtheoretical model [20], and the Person, Extended Family, Neighborhood model [21]. Constructs from these models influence the PTSC Program’s underlying theory of change: by convening women in supportive Sister Circles led by a racially and socioeconomically concordant facilitator, participants will engage in peer learning and will initiate and maintain relationships with women in their community who are embarking on similar health journeys. This will lead to 1) improved knowledge, attitudes, and beliefs about hypertension and cardiovascular disease risk management, 2) improved self-efficacy related to adherence to pharmacological and lifestyle-based antihypertensive regimens, 3) individual, familial, and community capacity around hypertension prevention or management, and 4) improved blood pressure management among mid-life Black women, thereby reducing seemingly intransigent disparities observed within this population (explicated in Fig. 3). Its conceptual roots are consistent with empirical work documenting the importance of social support and social circles in promoting positive health changes among AA women [22–24].

**Fig. 3 Fig3:**
[figure not shown]
Logic Model for PTSC-RCT

### Study design

The PTSC study is a randomized controlled trial that aims to 1) estimate the effectiveness of PTSC compared with usual care on blood pressure control among hypertensive, low-income, mid-to-late life AA women; 2) estimate the effectiveness of PTSC on health knowledge, health self-efficacy, and health behaviors that contribute to risks associated with hypertension; and 3) test whether there is a cost offset of PTSC for society. The PTSC RCT was approved by the Institutional Review Boards (IRBs) of the Johns Hopkins Bloomberg School of Public Health (JHBSPH) and the American Institutes for Research (JHBSPH IRB No. 00007121).

### Hypotheses

We hypothesize that patients randomized to PTSC will have better-controlled blood pressure than patients who receive usual care at the end of the intervention (13 weeks) and up to one-year post-intervention (15 months). We expect patients randomized to the PTSC intervention to demonstrate a more significant increase in health knowledge, hypertension-related locus of control, physical activity, medication adherence, and stress management practices than patients receiving usual care. Finally, we anticipate that patients randomized to PTSC will have fewer hospitalizations and emergency rooms visits for cardiovascular-related events than patients receiving usual care, and that the costs of providing PTSC will be offset by reductions in healthcare costs associated with health improvements for patients randomized to PTSC, compared to patients receiving usual care.

### Study population and eligibility criteria

We plan to recruit up to 440 AA women receiving care at Unity Health Care (Unity), a Federally Qualified Health Center (FQHC) in Washington, D.C. and Baltimore Medical System Incorporated (BMSI), a FQHC with practices in Baltimore, Maryland. Eligible patient participants include English-speaking women who self-identify as AA, are 40 to 75 years old, have uncontrolled hypertension (previously defined as systolic blood pressure ≥ 140 mmHg or diastolic blood pressure ≥ 90) [2, 25], and receive their primary care at a Unity Health Care practice or a BMSI practice. Participants will be randomly assigned to receive the PTSC intervention or usual care at Unity or Baltimore Medical System Inc.

Thus far, we have recruited 341 participants into the study (PTSC intervention arm = 216; usual care arm = 125; see Fig. 1), all of whom receive care at Unity Health Care and live in metropolitan Washington D.C. In the next phase of the study, we will recruit an additional 100 AA women residing in Baltimore, Maryland and receiving care at a BMSI practice. Of note, hypertension diagnosis guidelines have changed since the study’s inception, and hypertension is now defined as systolic blood pressure ≥ 130 mmHg or diastolic blood pressure ≥ 80 [25]. However, we are maintaining the same blood pressure thresholds as we had at the start of the study in order to maintain equivalence in evaluating program impact between cohorts over time, given that the previous hypertension diagnosis criteria were central to the study’s eligibility criteria and recruitment process. Moreover, the patients are currently being managed to meet the prior guidelines. Our criteria reflect the current designation for Hypertension Stage 2 [25].

### Power calculation

In order to detect a statistically significant difference in blood pressure control between the intervention and control groups post-exposure to the PTSC intervention, we need 440 participants (*n* = 220 per group) in our study. Our power calculations were based on the assumption of 80% HTN prevalence among study participants in both treatment arms at baseline, a two-sided alpha of 0.05, and a 15% reduction in the proportion of participants with high blood pressure after receipt of the PTSC intervention. The calculated sample size was 308, but our experience developing, implementing, and evaluating interventions with this target population suggests that we should anticipate a relatively high attrition rate. Thus, we computed a potential attrition rate of roughly 40%. In order to have sufficient power to detect a 15% reduction in HTN in the intervention group, we will recruit at least 40% above the estimated sample size, for a total sample size of 440 participants between Unity and BMSI health systems.

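### The required 308, the anticipated 40% attrition and the total of 440 do not reconcile: at 40% loss 440 leaves 264, and it keeps 308 only at 30% loss

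*Protocol article*

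**What the plan says.** The Power calculation section of the protocol article opens with the requirement: "we need 440 participants (*n* = 220 per group) in our study". Its inputs are "80% HTN prevalence among study participants in both treatment arms at baseline", "a two-sided alpha of 0.05", and a 15% reduction in the proportion with high blood pressure after the intervention. No power figure is given.

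The result before any allowance for loss is "The calculated sample size was 308". The allowance follows: "Thus, we computed a potential attrition rate of roughly 40" per cent. The section then links the two: "we will recruit at least 40% above the estimated sample size, for a total sample size of 440 participants". It presents this total as the number that gives sufficient power.

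The Study population and eligibility criteria section treats the same figure as a ceiling: "We plan to recruit up to 440 AA women". It reports enrolment so far as "PTSC intervention arm = 216; usual care arm = 125", which is 341 women, with a further 100 to come from Baltimore.

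**The concern.** An attrition rate is the proportion of recruited women who are lost. Allowing for it means dividing the required number by the proportion retained, not adding the same percentage to the required number. The section names 40% both as the attrition rate and as the minimum addition to 308, and the two are not equivalent. If 40% are lost, the trial does not end with the 308 that its own calculation requires.

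At stake is how the result is read. The article says 440 is enough to detect the planned effect. If the trial meets its own attrition assumption and finds no difference, readers would judge that result against more power than the design gives.

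Two details in the same calculation affect any restatement. The planned arms of 220 are hard to square with 216 and 125 already enrolled. The 15% is not labelled as absolute or relative.

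**Working it through.** **Inputs.** From Power calculation: 308 required, 440 planned, about 40% attrition, 80% with high blood pressure in both arms at baseline, a 15% reduction, two-sided alpha 0.05. From Study population and eligibility criteria: 216 and 125 enrolled, 100 to come. My assumptions: the usual-care proportion stays at 80%, and loss is equal in the two arms.

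**1. Reproducing 308.** Take 80% versus 65%, so d = 0.15 and p̄ = 0.725. The pooled two-proportion formula is

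n per arm = [1.96√(2p̄(1−p̄)) + z_power √(p₁(1−p₁) + p₂(1−p₂))]² / d²

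- 80% power: 138 per arm, 276 in total.
- 80% power with continuity correction, n/4 × [1 + √(1 + 4/(nd))]²: 151 per arm, 302 in total.
- 85% power, uncorrected: 158 per arm, 316 in total.

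So 308 is reproduced to within 3% as 15 percentage points, either at 80% power with correction (302) or at 85% without (316). A relative 15% reduction (80% to 68%) needs 418 at 80% power, or 450 with correction, and does not reproduce 308. The 15% is therefore taken as absolute.

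**2. Reproducing 440.**

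- 308 × 1.40 = 431.2, and 440/308 = 1.43, which fits an addition of at least 40%.
- 308/0.70 = 440 exactly, which fits a correct inflation for 30% loss.

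**3. What 440 retains.**

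| Attrition | Retained from 440 | Recruits needed to keep 308 |
|---|---|---|
| 30% | 440 × 0.70 = 308 | 308/0.70 = 440 |
| 35% | 440 × 0.65 = 286 | 308/0.65 = 474 |
| 40% | 440 × 0.60 = 264 | 308/0.60 = 514 |

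At 40% the shortfall is 308 − 264 = 44 retained women, or 514 − 440 = 74 recruits.

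**4. Power with equal arms, 80% versus 65%.** Power = Φ[(0.15 − c − 1.96·s₀)/s₁], where s₀ is the pooled standard error, s₁ the unpooled one, and c is 0, or ½(1/n₁ + 1/n₂) with continuity correction.

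- 154 per arm (308): s₀ = 0.0509, s₁ = 0.0502. Uncorrected 84.2%; with c = 0.0065, 80.9%.
- 132 per arm (264): s₀ = 0.0550, s₁ = 0.0542. Uncorrected 78.2%; with c = 0.0076, 73.9%.

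**5. Arm sizes.** Exactly 220 per group would need 220 − 216 = 4 more women in PTSC and 220 − 125 = 95 more in usual care. The article does not give the allocation ratio for the remaining women, so two assumptions are shown, each with 40% loss in both arms:

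- Last 100 allocated 1:1: 266/175, leaving about 160/105. Power 75.9% uncorrected, 71.2% corrected.
- Current split continues (216/341 = 63%): about 279/161 of 440, leaving about 167/97. Power about 74% uncorrected, 69% corrected.

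**The case against.** **The attrition figure may simply be misdescribed.** Because 308/0.70 is exactly 440, the total may be a correct inflation for 30% loss with 40% written by mistake, and 440 is indeed at least 40% above 308. This stands to the extent that the origin of 440 cannot be told from the article. A reader might infer that the authors certainly multiplied by 1.4, and the text does not prove that. On either reading the three printed figures conflict.

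**The effect is modest.** The 40% is hedged as potential and approximate, and at 35% attrition 286 women give about 81% power uncorrected. The cost at 40% is 6 to 7 points. The planned analyses are difference-in-differences and multivariable regression, so two-proportion power is only a proxy for the trial's sensitivity. All of this is fair, and it limits the consequence. It does not make the sample-size statement correct.

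**Stronger readings that the article does not support.**

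- That 220 per group is impossible: 4 and 95 more women make 99, and 100 are planned. Such a split is unlikely and none is described, but without a stated allocation ratio it is not excluded.
- That the 15% reduction is false: it holds as 15 percentage points. The wording is ambiguous, not wrong.
- That the 113 of 216 women who did not receive the intervention as designed (Discussion) show attrition above 40%: attending too few sessions is not the same as missing outcome data, and those women are not counted as lost here.

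**Conclusion.** The point holds for the Power calculation section as written. The shortfall of 44 at 40% attrition follows from the article's own 308, 40% and 440, and needs no outside assumption. Any attrition above 30% leaves fewer than 308, and the ceiling of 440 leaves no room to reach 514.

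The power figures are conditional. The article gives no target power, so they rest on 80% versus 65%, two-sided alpha 0.05, a two-proportion test and equal loss in both arms. With equal arms, power at 40% attrition is about 74% to 78%, according to whether a continuity correction is used, against 81% to 84% for the full 308. With arm sizes that follow from current enrolment it is about 71% to 76% (last 100 allocated 1:1) or 69% to 74% (current split continued). The loss is moderate, but under each of these assumptions power falls below the conventional 80%.

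**What to change.** Keep 440 and restate what it delivers. Suggested content for the Power calculation section:

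- 440 women retain 308 at 30% attrition and 264 at 40%.
- With 264 in equal arms, power is about 74% to 78% for an absolute difference of 15 percentage points (80% versus 65%) at two-sided alpha 0.05. Choose one method, name it, say whether a continuity correction is used, and print the single matching figure.
- State the target power behind 308, and that the 15% is absolute.
- Replace 220 per group with expected arm sizes, and state the allocation ratio for the remaining women. If it is 1:1, the arms are about 266/175 and power at 40% attrition is about 71% to 76%. If the current split continues, they are about 279/161 and power is about 69% to 74%.

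If 30% was the attrition actually used, correct that percentage and show 40% as the less favourable case. If 308 must be protected at 40%, the alternative is to recruit 514, which is 74 more women.

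Keeping 440 costs wording only: no change to design, recruitment or analysis, and a slightly less favourable power statement.

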### Study partners

This study is a collaboration between the Johns Hopkins School of Public Health Hopkins Center for Health Disparities Solutions (JHCHDS), the American Institutes for Research (AIR), the Gaston and Porter Health Improvement Center, Inc. (GPHIC), Unity Health Care (Unity), and Baltimore Medical System, Incorporated (BMSI). The PTSC Study was approved by the JHSPH and AIR Institutional Review Boards (IRBs). JHSPH HCHDS oversees recruitment and data collection for the PTSC study. AIR is responsible for data entry and management. GPHIC provides the PTSC program, materials, facilitators, and experts for those in the intervention group. Unity Health Care and BMSI assist with study recruitment through mass mailings to patients matching the eligibility criteria and posting flyers within centers. They also work directly with the PTSC-RCT partners to provide health care utilization data.

### Recruitment and randomization

Recruitment procedures commenced in 2017 and will cease in 2022. In the first wave of recruitment, Unity Health Care generated a list of the names and addresses of patients across their practices who fulfilled the study’s eligibility criteria. Candidate participants received a letter describing the study, incentives for participation, contact information for whom to follow up with, and the dates and locations for the recruitment sessions. We have also relied on word-of-mouth and targeted recruitment at Unity’s practices: Unity providers supplemented recruitment efforts by handing out flyers to eligible patients. We will follow the same recruitment processes for our BMSI participants.

Recruitment sessions, which occur in both the morning and afternoon of the same day to maximize attendance, are held in local churches located in predominantly AA neighborhoods. Women are randomly assigned to attend a session designed for the treatment arm or the usual care arm. JHCHDS staff, who conduct the randomization, are blinded to which sessions are for either arm, and both receive identical recruitment sessions. Each session features two interactive presentations. The first presentation, conducted by the GPHIC, describes cardiovascular health disparities at large and the ramifications of hypertension within AA communities, and highlights core components of the PTSC program. The second presentation, given by the JHCHDS, explains the study’s goals, timelines, and data collection procedures, and walks participants through the informed consent process. Attendees learn of their assigned treatment arm after the presentations have been made. At that point, written consent to participate in the study is obtained from those who wish to be a part of the trial.

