### Baseline data collection

Upon consent, study participants complete a baseline survey composed of items measuring their health behaviors (including self-reported adherence, physical activity, and diet), psychosocial attributes (e.g., depressive symptomology, hypertension-related locus of control, and adaptive stress management techniques), perceived health status, and healthcare utilization.

Baseline measures of BP, waist circumference, height, and weight are also obtained. Blood pressure is assessed using a digital Omron 10 series device. Women are seated at rest for 5 min with their feet flat on the floor, and their arms raised at the heart level. Appropriate cuff sizes, based on each participant’s arm circumference, are attached to the device to detect their BP reading accurately.

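### The arm is carried by the recruitment session a woman is sent to before she attends or consents, so attendance and consent can select differently by arm; allocate individually within sessions for the Baltimore cohort

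*Protocol article*

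**What the plan says.** Under Recruitment and randomization, the article fixes the unit that carries the arm: "Women are randomly assigned to attend a session designed for the treatment arm or the usual care arm". Letters to clinic patients gave "contact information for whom to follow up with, and the dates and locations for the recruitment sessions". The mailed list was not the only source: "We have also relied on word-of-mouth and targeted recruitment at Unity’s practices", and providers also handed flyers to eligible patients. Sessions are held in local churches, "which occur in both the morning and afternoon of the same day to maximize attendance".

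The same section states safeguards. The staff are people "who conduct the randomization, are blinded to which sessions are for either arm, and both receive identical recruitment sessions". Attendees are told their arm only once the presentations are over, and written consent is taken after that. Under Baseline data collection, the survey and physical measures follow consent: "Baseline measures of BP, waist circumference, height, and weight are also obtained".

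The Power calculation section plans 440 women, 220 per group. The Study population section reports 341 recruited so far at Unity, 216 in the PTSC arm and 125 in usual care, with about 100 more to come from Baltimore. The article says the Baltimore cohort will be recruited by the same processes.

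**The concern.** The order of events is: random assignment to a session, attendance, presentations, disclosure of the arm, consent, baseline. Only women who complete the whole chain are observed. Two of its links can act differently in the two arms.

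- **Attendance.** The arms meet at different sessions. Who comes to a given session depends on its time, its place and who else is going. These need not be the same for the two arms, even though no woman knows the arm in advance.
- **Consent.** By this point the arm is known, so willingness to join can depend on it.

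Randomisation protects the comparison of women as assigned. It does not protect the comparison of women who turned up and then agreed, if turning up or agreeing differs by arm. Availability, transport, health and social ties plausibly relate to blood pressure and to later attendance. The planned difference-in-differences analysis removes a fixed baseline difference between arms, but not a difference in how two differently selected groups would have changed. Covariate adjustment helps only as far as the covariates capture the selection. A larger sample does not help.

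**Working it through.** **1. Planned ratio.** Power calculation section: 440 / 2 = 220 per group, that is 1:1. The article states no other ratio.

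**2. Observed split.** Study population section: 216 + 125 = 341, and 216/341 = 63.3% in PTSC.

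**3. Comparison with 1:1.**
- Expected per arm: 341 / 2 = 170.5.
- Excess in PTSC: 216 - 170.5 = 45.5.
- Standard deviation: sqrt(341 x 0.25) = 9.23.
- z = 45.5 / 9.23 = 4.93.
- Exact two-sided binomial p = 9.5e-7.

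This test treats women as independent. If companions attend together, counts vary more than the binomial allows and the p-value is too small. It shows that the consented numbers do not look like simple individual 1:1 allocation. It does not say why.

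**4. What each explanation would require.**

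| Explanation | Arithmetic | Requirement |
|---|---|---|
| Equal assignment, unequal loss before or at consent | 125/216 = 0.58 | Usual-care women reached the trial at 58% of the PTSC rate. If every woman assigned to PTSC had joined, 216 - 125 = 91 of 216 (42%) were lost from usual care |
| Session-switching alone | 45.5/170.5 = 0.267 | A net 45 to 46 women, about 27% of those expected in usual care, moved to PTSC |
| Unreported 2:1 ratio | 341 x 2/3 = 227.3 expected; p = 0.21 | The data fit |
| Unreported 3:2 ratio | 341 x 3/5 = 204.6 expected; p = 0.22 | The data fit |

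The first row covers both unequal session attendance and refusal after disclosure. The text alone cannot separate them, because it gives no number of women assigned to each arm before attendance. Figure 1 is not visible here and may show it.

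**5. What can still be changed.** 440 - 341 = 99, which agrees with the stated 100. If 100 Baltimore women were split equally, the totals would be 216 + 50 = 266 and 125 + 50 = 175. Balanced recruitment in Baltimore would not restore 220 per group, but it would give 100/441 = 23% of the trial an allocation that attendance cannot influence.

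**6. The safeguards against each route.**

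| Route | Stated safeguard | Closed? |
|---|---|---|
| Staff steer women to an arm | Randomising staff do not know which session serves which arm | Yes |
| A woman knowingly picks her arm on first attendance | Identical sessions; arm told only at the end | Yes |
| Different women can or do attend each arm's session | None stated | No |
| Consent depends on the arm | None; consent follows disclosure | No |

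**The case against.** The strongest case against is that the article describes a real random assignment with sensible masking, reports no woman attending a session she was not assigned to, and as a condensed account may leave attendance checks and the handling of word-of-mouth recruits to the full protocol. That stands as far as it goes. The silence on those checks is not the point made here. The point is the stated design: arm-specific sessions, assignment before attendance, and disclosure before consent.

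Three stronger readings are tempting, and the documents do not support them.

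- **Allocation was broken by women coming to another session.** A reader might infer this from the mailed dates, the word-of-mouth recruits and the 216 to 125 split. The text does not say whether a letter listed sessions other than the assigned one, or that word-of-mouth recruits bypassed randomisation. The split has other explanations.
- **Offering morning and afternoon sessions shows that women could choose their slot.** It does not. Two slots could also serve each arm or simply add capacity.
- **Baseline blood pressure was taken at different times of day in the two arms.** No sentence links a slot to an arm. If each arm used both slots there would be no offset, so no bias can be sized from this document.

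It is also fair to say that consent after disclosure could account for the imbalance on its own. That does not rescue the design. It belongs to the same sequence, and the same change removes it.

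**Conclusion.** The concern holds as a weakness of a stated design choice, not as a documented breach. Because the arm belongs to a session and is made known before consent, the women who enter each arm are those who came to that arm's session and then agreed. The blinding and the identical presentations rule out knowing choice at first attendance. They leave open self-selection through attendance and arm-dependent loss before consent.

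The 216 to 125 split shows that the process is not delivering the planned 1:1 numbers. That conclusion assumes that 1:1 was the intended ratio throughout and that women can be treated as roughly independent. The size and direction of any resulting bias in the blood pressure comparison cannot be derived from the article, and no figure is offered. The matter should be acted on because about 100 women are still to be recruited by the same process.

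**What to change.** **Baltimore cohort (about 100 women).** Stop using arm-specific sessions.
1. Let any eligible woman attend any session.
2. Take consent and all baseline measures first.
3. Then allocate each woman individually within the session, from a pre-generated, concealed central list with varied block sizes.
4. Disclose the arm to each woman individually.

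A woman who withdraws on learning her arm is then a counted, randomised participant with baseline data.

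**Unity cohorts (341 women).** Analyse each woman by the arm recorded for her on the randomisation list, whichever session she attended. Add a sensitivity analysis excluding any woman with no assignment recorded before attendance. If Figure 1 does not already do so, report by arm the numbers assigned, attending and consenting, and state the intended ratio. This would show which explanation in the working applies. These steps deal with switching and unassigned attendees. They cannot recover women who were assigned but never consented, so that limitation should be acknowledged.

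**Cost.** Revised protocol wording with the usual ethics approval, one allocation list, and one sensitivity analysis from existing records. The main downside is practical: women in the same session will receive different assignments, so disclosure must be individual.
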